Signing of informed written consentClinical data will be collected in a questionnaire specifically designed for this study:o Sociodemographic variables: age, sex, education (years and level of education), hand dominanceo Anthropometric variables: height, weight.o Vascular risk factors: smoking habit (never, current, former), alcohol intake, physical activity level (sedentary, home-activity, outdoor activity and grade), history of hypertension, diabetes mellitus, dyslipidemia, and arrhythmia (atrial fibrillation or another type).o Current drug intake (platelet inhibitors, anticoagulants, lipid-lowering drugs, antihypertensives, hypoglycemic agents, antiarrhythmics, antidepressants).o Vascular events presented prior to inclusion in the study: angina, myocardial infarction, intermittent claudication, transient ischemic attack, and stroke.o Heart Failure: Using the New York Heart Association classification (From class I to IV)o Renal function before treatment (creatinine level and glomerular filtrate)o Total score in EuroScore II  [32]3Neurological evaluationA complete neurological evaluation will be carried out by a neurologist specialized in cerebrovascular diseases. It will include; a complete anamnesis and review of the subject’s clinical history, including data from neuroimaging studies to confirm the existence of previous cerebrovascular pathology in any of its manifestations (Type 1: overt Central Nervous System (CNS) injury; Type 2: covert CNS injury, and Type 3: neurologic dysfunction without CNS injury) following the Neurologic Academic Research Consortium  (NeuroARC) recommendations [33]. Likewise, a neurological examination will be carried out using the National Institutes of Health Stroke Scale (NIHSS) [34] to detect neurological deficit attributable to cerebrovascular lesions, with a score range of 0 to 42, with 0 indicating absence of focal neurological damage. Functional dependence will be assessed with the modified Rankin scale (mRS) ranging from 0 to 6, where 0 indicates functional independence and 6 death [35]. In addition, depressive symptoms will be assessed with the Geriatric Depression Scale (GDS), with scores higher than five indicating probable depression [36], and cognition will be assessed by the Informant Questionnaire On Cognitive Decline in the Elderly (IQCODE) test with scores higher than 57 indicative of probable cognitive decline [37]. The same stroke neurologist will assess all cerebrovascular events that subjects may experience during follow-up.4Neuropsychological assessment:Acquisition, analysis of neuropsychological variables:

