### Statistical considerations

The sample size calculation will be based on the main variable of the study, Impairment Index or Global Cognitive Impairment Index, which will be handled as a standardized normal distribution (mean=0 and SD=1). The way to transform the values of every subject to a standardized value is using the formula (value-mean)/SD. With this approach, we can estimate the difference between groups as a difference in the standardized normal distribution (z score), avoiding to approximate or guess values of SD that we do not previously know.

Establishing an alpha error of 5% and a beta error of 20% (80% statistical power), for a two-sided analysis and an effect size to observe defined as a minimal difference in z score of 0.67. Applying these criteria, an estimate of 36 patients per group is obtained. Assuming a loss of follow-up of 10%, we aimed to recruit 40 patients per group. The statistical package used for sample calculations was Stata 14.2 (StataCorp LLC, College Station, Texas, USA).

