A descriptive analysis of the sample will be carried out based on the characteristics of each variable. Continuous variables will be expressed as mean and 95% confidence interval, or median and interquartile range for each of the study groups, choosing the most appropriate description according to the result of the Shapiro-Wilk normality test. Categorical variables will be expressed with their absolute frequency (count) and relative frequency (as a percentage).Data cleansing and exploration of missing values will be carried out. Missing data greater than 10% will be considered excessive, deciding whether to maintain the variable in the study according to its importance in the literature and in the study design. For missing data recognized as excessive in clinically important variables, the dataset will be completed using multiple imputation techniques. Student t-test will be preferred for the crude comparative analysis between groups as a bilateral parametric test that will allow us to find differences in both directions of the hypothesis, given the heterogeneity of the existing literature. Equality of variances will be tested using the Levene test to adjust the standard error in the comparison. Sample size should ensure the conditions of application of parametric tests.The statistical adjustment of confounding factors and interaction of predictors will be carried outby building an explanatory model using multivariate linear regression, thus obtaining the coefficient corresponding to the main variable adjusted by the rest of potentially confounding or effect-modifying variables. First, a univariate screening of variables will be carried out, introducing in the model those which present confounding criteria based on the Pearson correlation test. Subsequently, first-order interactions will be explored based on statistical significance tests. The adjustment of confounding factors will be carried out based on relevant modification criteria (larger than 10%) of the model coefficients, according to the methodology described by Kleinbaum et al [58], and applying the principle of parsimony. The search for independent predictors of neuropsychological dysfunction will be carried out using a predictive approach of hierarchical logistic regression with a stepwise backward methodology.An analysis of residuals and extreme values will be carried out to verify the robustness of the built model. For the rest of the secondary hypotheses, mean comparison techniques (Student's t-test with adapted standard error) and proportions (chi-square) will be used.

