Probably one of the most critical points in the evaluation of cognitive impairment is the selection and design of the neuropsychological test battery. Studies differ with regard to the neuropsychological tests used, making it difficult to establish meaningful comparisons. Despite the profile of cognitive impairment after AVR is VCI, somestudies use only one or two screening tests, usually the MMSE [22, 23], which lacks adequate sensitivity to detect VCI. Other studies use the MoCA, which is more sensitive to VCI but still provides only a brief and limited measurement of cognitive function [24, 25]. Only a complete NRP battery that includes all the necessary domains may be able to detect cognitive impairment following the procedures, which might otherwise go undetected.. Some studies analyze the correlation between specific cognitive domains affected by VCI and subcortical vascular insult. For example, ischemic lesions in prefrontal-subcortical circuits have been associated with lower executive function, forgetfulness and changes in speech and emotion [60]. Some studies have explored these cognitive domains after TAVI, but the results were not homogeneous. A study that measured changes in delayed recall, working memory, verbal learning, and fluency immediately and three months after TAVI did not find significant differences [68]. Another study showed that visual attention and delayed recall improve at the early follow-up after TAVI [69]. On the other hand, a study that assessed changes in executive function, processing speech, and abstract reasoning demonstrated that about 25% of the subjects had an early decline in these domains, which remained at 40% at 1-year follow-up [70].

We would like to point out that together with the pre-existing cognitive impairment and the characteristics associated with the procedures, the other variable associated with cognitive changes in AVR is age. In older patients, the impact of cognitive impairment after AVR is particularly important because it may increase their morbidity and lower their quality of life. Interestingly, there is one study that demonstrated increasing older age as the only independent risk factor for cognitive impairment after TAVI, but not the other factors as cognitive status, prior stroke events, use of embolic protection devices, or silent cerebral lesions. [71].

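### Choosing independent predictors by backward stepwise logistic regression in about 72 patients carries a high risk of spurious or unstable results

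*Protocol article*

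**What the plan says.** The Statistical considerations section of the protocol article describes two regression exercises. One is a linear explanatory model for the adjusted group effect, with univariate screening, a 10% change-in-coefficient rule and parsimony. The other is a separate search for independent predictors of dysfunction on the neuropsychological tests, to be done "using a predictive approach of hierarchical logistic regression with a stepwise backward methodology". For this second model the article gives no candidate list, removal threshold, expected number of events, shrinkage or internal validation. The one check mentioned is an inspection of residuals and extreme values.

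The sample size serves the primary comparison only. It rests on "an effect size to observe defined as a minimal difference in z score of 0.67" with SD 1, from which "an estimate of 36 patients per group is obtained". The section continues: "Assuming a loss of follow-up of 10%, we aimed to recruit 40 patients per group".

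The section on baseline procedures lists many variables, for example "Vascular risk factors: smoking habit (never, current, former), alcohol intake, physical activity level", along with drug classes, prior vascular events, renal function and clinical scales. Procedural and MRI measures are listed elsewhere. The only rates of cognitive decline in the article come from a cited study, in the Discussion: "about 25% of the subjects had an early decline in these domains, which remained at 40% at 1-year follow-up".

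**The concern.** Backward elimination starts from a full model and removes the weakest term until every remaining term passes a threshold. When events are few relative to candidates, three things go wrong. Noise variables survive by chance. The chosen set changes with small changes in the data. The final p-values and intervals are computed as if the surviving terms had been named in advance, so they look more certain than they are.

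The criticism is of a method that the article states, not of missing detail. A fuller document could add a candidate list or a threshold, but it could not drop backward logistic selection without departing from this text. The abstract hopes that the results may help fit interventions to the individual, and the article aims to inform Heart Team decisions. Variables reported as independent predictors are the kind of result that readers would carry into such decisions.

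**Working it through.** **1. The plan's own figure.** Inputs from Statistical considerations: "Establishing an alpha error of 5% and a beta error of 20% (80% statistical power), for a two-sided analysis", difference 0.67, SD 1.
- Normal approximation: n = 2 × (1.96 + 0.84)² / 0.67² ≈ 35 per group.
- The t-test version gives 35.96, so 36 per group, with power 80.05%.
- 10% loss: 36 / 0.90 = 40 per group, 80 in total.

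The stated figures reproduce. They concern a comparison of two means and say nothing about a multivariable logistic model.

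**2. Events.** Evaluable patients: 2 × 36 = 72.
- Ceiling for the smaller outcome class: 72 / 2 = 36.
- At 25%: 72 × 0.25 = 18.
- At 40%: 72 × 0.40 = 28.8, about 29.

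The 25% and 40% are assumptions, borrowed from the study cited in the Discussion. The ceiling of 36 needs no such assumption.

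**3. Candidates.** The baseline questionnaire gives 29 variables: 4 sociodemographic, 2 anthropometric, 7 vascular risk factors, 7 drug classes, 5 prior events, NYHA class, 2 renal measures and EuroScore II (4 + 2 + 7 + 7 + 5 + 1 + 2 + 1 = 29). Adding NIHSS, mRS, GDS, IQCODE, MMSE and MoCA gives 35, and treatment group makes 36. The article does not say which of these are candidates, so a range is shown.

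**4. Events per variable** = events / candidates, one coefficient each:

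| Candidates | 18 events | 29 events | 36 events |
|---|---|---|---|
| 5 | 3.6 | 5.8 | 7.2 |
| 10 | 1.8 | 2.9 | 3.6 |
| 20 | 0.9 | 1.4 | 1.8 |
| 36 (all listed) | 0.5 | 0.8 | 1.0 |

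**5. Noise retained.** Simulation: 72 patients, independent pure-noise candidates (half continuous, half binary), backward elimination at p<0.05 (assumed, since the article gives no threshold), 400 runs per cell. Share of fitted runs ending with at least one false predictor:

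| Candidates | 18 events | 29 events | 36 events | 1 − 0.95^k |
|---|---|---|---|---|
| 5 | 19% | 20% | 25% | 23% |
| 10 | 37% | 40% | 41% | 40% |
| 15 | 48% | 56% | 53% | 54% |
| 20 | 57% | 68% | 70% | 64% |

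With 400 runs the Monte Carlo standard error is at most √(0.5 × 0.5 / 400) = 2.5 percentage points. The last column, the chance of at least one p<0.05 in k independent tests, shows that most of the false-positive rate comes from the number of candidates tried.

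With all 36 as candidates, the fit failed in 95%, 68% and 56% of runs at 18, 29 and 36 events. In that case the backward procedure often could not be completed.

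**The case against.** The strongest reply is that the baseline list is an inventory of collected data, including height and hand dominance, and not a list of candidates. The word hierarchical may mean ordered blocks, and a condensed article may leave the list to a fuller document. This stands against one tempting inference, that there will be at most about one event per candidate. That figure needs every listed variable to be a candidate, which the article does not say. With 10 candidates the ratio is 1.8 to 3.6. The reply does not remove the problem, because 10 noise candidates already give about a 40% chance of a false predictor, and entering variables in blocks does not correct for selection.

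A reader might also infer that the analysis will certainly report false predictors. The simulation does not show this. It gives about 19-25% with 5 candidates, and all its figures assume that nothing truly predicts, whereas the Discussion treats age and pre-existing impairment as related to cognitive change.

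The event rates are uncertain too. They come from a study of selected cognitive functions, and the 40% could be read as persistence among those who declined early. On that reading there would be only 18 × 0.40 = 7.2 events at one year.

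Nor does the article say that the GCII will be dichotomised. It separately defines mild and moderate impairment by domain cut-offs of 1.5 and 2 SD, and the outcome of the logistic model is tied to neither.

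Finally, the predictor search is not among the four specific objectives in the Background, and the claim about individual tailoring is cautiously worded. Both points limit the weight of the concern without answering it.

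**Conclusion.** The concern holds in a bounded form. The article fixes a selection method that 72 evaluable patients, with at most 36 in the smaller outcome class, support poorly. For 10 to 20 candidates there would be about 0.9 to 3.6 events per variable. If no candidate predicts, the chance of keeping at least one noise variable is about 40% with 10 and 57-70% with 20. Only if all 36 listed variables were candidates would the ratio fall to 0.5-1.0, and then the model would often fail to fit.

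These figures rest on an assumed threshold of 0.05, on independent noise candidates and, below the ceiling of 36 events, on borrowed event rates. The planned check of residuals and extreme values detects neither overfitting nor selection bias, and the screening and parsimony rules are described for the other model. This is a secondary analysis, and the primary GCII comparison is untouched.

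**What to change.** Replace the backward stepwise step with a short predictor set, about 4 to 6 terms, that the investigators choose on subject-matter grounds and fix before the analysis. Retain all terms and report them all. Preferably fit them in a linear model for the continuous GCII, which uses all 72 outcomes: 72 / 6 = 12 to 72 / 4 = 18 patients per term. If the binary impairment classification is kept, state its cut-off and visit and use a penalised (ridge or Firth) logistic model, because 18 / 6 = 3 to 29 / 4 ≈ 7 events per term is still few. Add bootstrap optimism correction and label the analysis exploratory.

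This does not abolish chance findings. With 4 to 6 independent null terms, the chance of at least one p<0.05 is still 1 − 0.95⁴ = 19% to 1 − 0.95⁶ = 26%. However, the number of terms tested is then visible, and the intervals are no longer conditional on an unreported search. The cost is a change of wording and fewer predictors examined. No extra patients or data are needed.

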## Background

Degenerative aortic stenosis (AS) is the most common valve heart disease among older patients in developed countries, with an exponential increase in prevalence with age. A meta-analysis conducted in those countries found a population prevalence of AS and severe AS in those aged 75 years and older of 12.4% and 3.4% respectively [1, 2].

Surgical aortic valve replacement (SAVR) has been the treatment of choice for patients with severe AS, but it is not appropriate for high-risk patients. In this scenario, over the past decade, several randomized controlled trials and observational studies have established the non-inferiority and even superiority of transcatheter aortic valve implantation (TAVI) compared with SAVR in high-risk patients or those considered inoperable [3–6].

Improvement in the learning curves of the endovascular technique, in the devices, and in the access routes have led to the indication of TAVI in intermediate-risk patients [7–9]. For this reason, nowadays-international guidelines have recommended the use of TAVI in inoperable and high-risk patients (Class I) and in intermediate-risk patients (Class IIa) [10–12].

Previous results and the minimally invasive technique of the TAVI procedure have encouraged investigations, as the recently published PARTNER 3 and Evolut Low-Risk trials [13, 14], showing non-inferiority and even superiority of TAVI compared with SAVR for some of the outcomes in low-risk patients.

Mortality and postoperative complications in patients undergoing aortic valve replacement are variable. In this study, we will focus on the most important and potentially disabling cerebral vascular events and vascular cognitive impairment (VCI).

In 2010 the PARTNER randomized trial showed a significant increase in stroke in the TAVI group compared with SAVR (5.5% and 2.4%) [4]. Two meta-analyses published in 2013 [15, 16] did not show significant differences (3.5 vs. 2.8% and 2.6 vs. 2.3%). Although the rate of stroke may have decreased marginally as TAVI has improved, questions continue to arise about the importance of microembolisms or silent cerebral infarcts that may cause changes in cognition. TAVI is associated with a high incidence (up to 84%) of silent cerebral embolism as detected by diffusion-weighted MRI (DW MRI) [17], more frequent than that following aortic valve surgery [18]. However, a clear correlation between the number or volume of vascular lesions and cognitive impairment has not been demonstrated.

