Advanced imaging studies, such as resting-state MRI (rs_MRI), is used in brain mapping to assess regional interactions that occur in a negative task. Several resting-state conditions have been identified in the brain, one of which is the Default Mode Network (DMN), which is more active during the rest period than during task execution. The Salience Network (SN) is key because it regulates the activation of the Central Executive Network (CEN) while deactivating the DMN during the execution of a task. In the case of cognition, it is interesting to study the integration of these different neural networks. Interestingly, a study on VCI found differences in rs_RNM between subjects with and without cognitive impairment, which also correlate with neuropsychological tests such as the Montreal Cognitive Assessment (MoCA) [30].

In this context of uncertainty regarding the clinical importance of stroke and VCI in patients that undergo SAVR and TAVI, we designed a prospective study called ARTiCO (Aortic valve Replacement compared to Transcatheter implant and its relationship with Cognitive impairment). The specific objectives are;(1) to compare the early and late cognitive changes after the intervention in both groups;(2) to compare the occurrence of stroke during follow-up in both groups;(3) to quantify and compare the appearance of silent vascular lesions in the MRI at follow-up in both groups;(4) to study with functional MRI, changes in brain activity and functional connectivity and to correlate them with NRP functioning.

Therefore, the study aims to provide relevant information to determine whether cognitive dysfunction appears, persists, increases or even decreases and whether it does so differently between the SAVR and TAVI groups. We also will study the clinical and silent incidence of cerebral vascular disease between both techniques. Finally, we will analyze the correlation between neuropsychological and neuroimaging approaches in order to evaluate cognition.

The final goal of the study is to gather evidence that will help the Heart Team in decision-making processes regarding which treatment to apply to patients with the indication of AVR. This article describes the ARTiCO study protocol.

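### New silent lesions get crude tests in a non-randomised cohort, and stroke is set up for a between-group test that the cited comparative rates cannot inform

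*Protocol article*

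**What the plan says.** The Background lists the specific objectives. The second is "to compare the occurrence of stroke during follow-up in both groups" and the third is "to quantify and compare the appearance of silent vascular lesions in the MRI at follow-up in both groups".

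Statistical considerations sizes the study on the Global Cognitive Impairment Index (GCII) alone. It then sets out the analysis in three steps:

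- A Student t-test for the crude comparison between groups.
- A multivariable linear regression to adjust the coefficient of the main variable for confounders and interactions. Logistic regression is mentioned only for predictors of neuropsychological dysfunction.
- A closing rule for everything else: "For the rest of the secondary hypotheses, mean comparison techniques" (Student's t-test "with adapted standard error) and proportions (chi-square) will be used").

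Stroke and silent lesions are not named in that section, so they fall under the closing rule. The design section says that the Heart Team assigns treatment and concedes that the study is not randomised. The Discussion nevertheless expects comparable groups, because only patients suitable for both techniques enter.

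**The concern.** Suitability for both procedures narrows the population. It does not balance age, surgical risk score, atrial fibrillation, previous stroke or existing vascular lesions between the groups. The plan accepts this for the GCII: its z scores use norms corrected for age and education, and a regression then adjusts for confounders. Lesion outcomes in the same patients get neither step, so a crude lesion difference may partly reflect who was sent to which procedure.

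Stroke has a different difficulty. At the comparative rates that the article cites, a study of this size will see very few events, so a test says little whichever way it falls. The stated purpose is to help Heart Teams choose a treatment. A chance imbalance of a few strokes, or an uninformative absence of difference, could be read as guidance.

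**Working it through.** **1. The plan's own figure.** Inputs, from Statistical considerations: "Establishing an alpha error of 5% and a beta error of 20% (80% statistical power" and "for a two-sided analysis and an effect size to observe defined as a minimal difference in z score of 0.67". With SD 1, n per group = 2 × (1.96 + 0.84)² / 0.67² ≈ 35 by the normal approximation. The t-test solution is 35.96, so 36, which matches "an estimate of 36 patients per group is obtained". Then 36 / 0.90 = 40 recruited. The figure reproduces, and it concerns the GCII only.

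**2. Which outcomes are adjusted.**

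| Outcome | Assigned method | Adjustment described |
|---|---|---|
| GCII | t-test, then linear regression | yes |
| Predictors of neuropsychological dysfunction | backward stepwise logistic regression | multivariable |
| Silent lesions (objective 3) | t-test or chi-square | none |
| Stroke (objective 2) | chi-square | none |

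The covariates exist already. The initial visit records age, sex, education, vascular risk factors, arrhythmia, previous vascular events, renal function and EuroScore II, and a baseline MRI is done.

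**3. Silent lesions.** The article cites up to 84% (Background) and 98% (Discussion) after TAVI, and up to 61% after SAVR (Discussion). These come from separate studies, so pairing them is an assumption. At 36-40 per arm:

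- 84% v 61%: 30-34 v 22-24 affected patients, expected lesion-free count 9.9-11.0 per arm, chi-square power 60-65%.
- 98% v 61%: 35-39 v 22-24 affected patients, expected lesion-free count 7.4-8.2 per arm, power above 99%.

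Expected counts exceed 5, so chi-square is valid as a test. Power is moderate to high, so a nominally significant crude difference is quite possible. That is why bias matters here.

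**4. Stroke at the Background rates.** The 2010 randomised trial "showed a significant increase in stroke in the TAVI group compared with SAVR (5.5% and 2.4" per cent respectively. Two meta-analyses gave 3.5 v 2.8% and 2.6 v 2.3%. Expected events = n × rate. Power comes from exact enumeration of all 2×2 tables, uncorrected chi-square, two-sided 5%.

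| TAVI v SAVR | Events at n = 36 | Events at n = 40 | Power |
|---|---|---|---|
| 5.5 v 2.4% | 1.98 v 0.86 | 2.20 v 0.96 | 6.2-7.6% |
| 3.5 v 2.8% | 1.26 v 1.01 | 1.40 v 1.12 | 1.9-2.4% |
| 2.6 v 2.3% | 0.94 v 0.83 | 1.04 v 0.92 | 1.0-1.3% |

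For 5.5 v 2.4%, 80% power needs about 600 per arm (595 by the arcsine formula, 619 by the usual two-proportion formula). With 2 v 1 events in 36 each, the Newcombe 95% CI for the difference runs from about -9 to +16 percentage points.

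**5. Stroke at the Discussion rate.** The Discussion also cites 17% clinical stroke after SAVR, giving 36 × 0.17 = 6.1 to 40 × 0.17 = 6.8 events. With TAVI assumed at 5.5%, 3.5% or 2.6%, chi-square power is 37-40%, 53-57% or 61-66%.

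**6. Size of the chi-square test.** With the same stroke rate in both arms, between 2.4% and 5.5%, the true type I error is 0.9-4.8%. At 10% it is 5.8-5.9%, and at 17% it is 5.1-5.2%.

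**The case against.** The strongest reply is that these are secondary objectives in a condensed article, that the sample size claims power only for the GCII, and that outcome-specific models belong in a fuller document. Part of this stands: the article never claims power for stroke, and it admits that allocation is not random. But the closing rule is a stated choice of method, not a gap. One could also take the main variable in the adjustment paragraph to be treatment, so that the regression might serve any outcome. Even so, a linear model does not suit stroke or lesion presence, and the last sentence gives the remaining hypotheses their own, unadjusted methods.

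A reader might infer more than the document supports:

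- **That chi-square p-values for stroke are unreliable and Fisher's test is required.** Single tables do differ: 4 v 0 in 36 each gives p = 0.040 by chi-square and 0.115 by Fisher. But at common rates of 2.4-5.5% chi-square stays below 5%, and at 10-17% it exceeds 5% by less than one percentage point. Fisher would cut power at 5.5 v 2.4% from 7.6% to 0.9% with 40 per arm. The test is not the main problem.
- **That silent lesions are also too sparse.** At 61-98% affected they are not.
- **That lesion counts have many zeros and a long tail, so a t-test fails.** The article gives no lesion distribution.
- **That every cited rate gives 1 to 2 strokes per arm.** The 17% SAVR rate does not, and it comes from studies with neurological adjudication and brain imaging, close to what is planned here.

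**Conclusion.** The point holds for two things. First, the plan compares silent lesions without adjustment in groups formed by clinical decision, although it adjusts the GCII in the same patients. The direction and size of the bias cannot be given, since the article shows no baseline data by group.

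Second, the stroke comparison carries very little information at the article's comparative rates: 0.8-2.2 events per arm and 1-8% power. In the most favourable cited scenario power is still only 37-66%, below 80%.

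This assumes 36-40 patients per arm, that the cited rates apply to this population over one year, and, for the 17% scenario, a TAVI rate of 2.6-5.5%. That pairing mixes sources whose ascertainment may differ.

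**What to change.** **Silent lesions.** Replace the closing rule for objective 3 with adjusted regression: a logistic model for new-lesion presence, and a model suited to the observed scale for number or volume. Adjust for baseline lesion load and the same confounders as the primary model. At the cited rates only about 15-22 patients in total would be lesion-free (twice 7.4 to twice 11.0), so the presence model needs a short covariate list or penalised estimation. The crude comparison can stay beside it.

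**Stroke.** Report counts per group and the risk difference with an exact or score 95% CI, label the analysis descriptive, and state that no conclusion of difference or equivalence will be drawn.

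**Cost.** Slightly more analysis work on data already collected, and a more modest stroke objective. No change to sample size, visits or measurements.
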